## 3. Factor of Interest

### 3.1. Environmental

Birthing delivery mode, method of infant feeding, and introduction of solid food and allergen to the infant diet could represent potential environmental factors causing ASD, so these will be recorded for each enrolled participant [53,62,63]. A diary of antibiotic usage will be completed by the parents monthly for the first year of life, and food diaries completed at the same time points will assess duration of breastfeeding (or other preferred feeding mode).

After the first year of life, detailed, although less frequent, records of antibiotic use will be obtained with each stool sample for the remaining duration of the study. Although the food diary will be discontinued at this time, pertinent dietary habits of both the mother and child will continue to be carefully recorded approximately every six months.

Moreover, details such as antibiotic exposure in early infancy, family living address, exposure to pets, and gastrointestinal sporadic symptoms will also be recorded.

### 3.2. Genetics

Currently, ASD heritability based on mono- and dizygotic twins is estimated to be about 79–80% [64,65]. Concordance is higher in monozygotic twins than dizygotic twins.

First-degree relatives of ASD probands show behavioral or cognitive features associated with autism intensification, such as language and social dysfunction, albeit in lesser forms [66], known as “broader phenotype” [67,68,69,70].

ASD-related social impairments are heritable [71] and increase in unaffected parents and children of autistic probands [72]. Several studies evaluating sub-threshold ASD traits in population cohorts suggested that different components, separately representing language, social function, and repetitive or stereotyped behaviors contribute to ASD [73,74,75]. Globally, these results suggest that ASD features represent a continuum of function that may be inherited in distinct patterns. This is consistent with the knowledge that specific genetic factors contribute to the development and function of specific brain structures, and that distinct brain circuits may underlie different components of autism [76].

Moreover, several genetic syndromes, including Fragile X, Tuberous Sclerosis, Joubert Syndrome and Smith Lemli Opitz, are known to cause, although with low penetrance, ASD-like symptoms [76,77]. This evidence further favors a genetic cause for ASD [78].

To assess the contribution of genetic risk factors, in combination with exposure and other omics data, we will perform whole genome sequencing in all participants with ASD, in addition to their parents. This will enable investigation of both common and rare variants that contribute to ASD risk.

### 3.3. GI Microbiome and Metabolome

The complete understanding of the host-GI microbiome genomics is necessary for the prediction of the activation of metabolic pathways linked with functional and clinical outcomes. Urine and stool samples will be collected and analyzed for a metabolomic phenotype of the GI microbiota and metabolomics profiles, including metabolites linked to bacterial activity in ASD. The metabolomic profiles, exploratory semi-quantitative assays, and targeted quantitative assays will be conducted throughout the study. Systems models of integrated metabolomic phenotypes will be created with the statistically linked data between the microbiota and immune function. By conjoining microbiota data and metabolomic data we will be able to understand the functions associated with GI comorbidity of children with ASD and the ASD patient-derived microbiota. Dietary interventions with pre/pro/synbiotics will be created based on the results found in the humanized mouse models undergoing fecal transplantation with ASD-specific microbiota.

### 3.4. Immune Function

The peripheral blood mononuclear cells (PBMCs) will be harvested and studied for immune functions. Standard flow cytometry will be used to measure monocyte and T-cell intracellular cytokine patterns. By looking at the T cell populations in children with ASD with and without GI symptoms we will be able to understand what cellular activation and functional alterations are present. Assays performed on serum samples collected at clinical visits include: serum zonulin determination; serum IgA and IgG anti-gliadin and anti-casein determination by the ELISA method; serum pro-inflammatory cytokines, including IL-1, TNF, IFN, IL-10, IL-12, IL-6, IL-15, and IL-8 by Bioplex assay; and cytokine gene expression by RT-PCR. Protein glycosylation is directly involved in nearly every biological process presenting altered glycosylation as potential biomarkers in many human conditions including inflammation, diabetes, rheumatism, cancer, and neurological disorders [79]. Serum immunoglobulin glyco-signaturing will be performed using lectin microarrays and anti-glycan ELISA profiling. Saliva samples will also be analyzed for proinflammatory cytokines and inflammatory markers selected from a previous study [61], and altered glycan and glycation products.

## 4. Statistical Approach

### 4.1. Statistical Methods

Categorical data will be described using frequency counts and percentages, and continuous data with mean, standard deviation, median, minimum, and maximum. Both parametric and non-parametric methods will be used to analyze the data. All omics data will be preprocessed with appropriate methods. The multi-omics analyses will be performed with statistical tests, regression models, and more advanced methods such as sparse canonical correlation analysis and random forest analysis. The false discovery rate (FDR) method will be used to adjust the *p*-values for multiple comparisons. Statistical significance will be set at *p* < 0.05.

### 4.2. Power Analysis

We estimated a conservative drop-off of 20% based on our previous experience with similar projects involving two cohorts of infants at-risk of celiac disease, one that has been followed for 10 years with a 20% drop-off [52] and a second that has been followed up to 7 years with a 12% drop-off [53]. The final cohort will comprise approximately 500 at-risk infants. Expected prevalence of ASD at 18–24 months in first-degree relatives is 14.7% [9], so in this study we estimate 73 ASD diagnoses. The expected prevalence of GI symptoms in an ASD population is 60% [80], so we anticipate 44 of the 73 ASD diagnosed infants to also present GI symptoms.

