### 2.2. Clinical Study

#### 2.2.1. Participants

GEMMA aims to enroll 600 infants younger than 6 months/26 weeks of age, who have an older sibling with ASD for the observational trial. The recruitment will be carried out in three different centers: Irish Center for Autism and Neurodevelopmental Research (ICAN) at the National University of Ireland, Galway, Azienda Sanitaria Locale Salerno (ASL), and satellite centers in Italy, and Mass General Hospital for Children (MGHFC) Lurie Center for Autism in USA. The first study samples must be collected prior to the introduction of solid foods. Children who have started any other therapeutic intervention for ASD will also be excluded from the study. According to our previous experience with similar projects involving two cohorts of infants at-risk of celiac disease [52,53], enrollment will be performed by inviting parents’ of the autistic patients who are followed by the recruitment clinics to participate in the study in the case of newborns, and advertising the study among ASD support and ASD patients’ groups. Moreover, a traditional and social media diffusion plan was created to increase the project knowledge and support. No compensation will be provided to the participant.

Infants aged 18–36 months who were recruited, completed the observational study, developed clinical signs and symptoms of ASD, and whose parents permit the intervention of solely dietary and oral therapy in this study, will be invited to enroll for a follow-on dietary interventional trial.

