#### 2.2.2. Observational Trial

This study phase will evaluate infants at high risk of ASD. To achieve the sample size needed for clinical and biological comparisons, and ensure there is a reasonable representation across study sites, each site will target recruitment of 200 infants at high risk of developing ASD, over a 3 year period. All recruited children will undergo regular clinical and laboratory evaluations for 36 months, or more in the case of ASD development based on the annual intermediate clinical data check. Blood, urine, stools, and saliva samples will be collected every 6 months until 36 months of age.

Regarding GI symptoms, children will be evaluated for chronic irregular bowel movements (constipation, diarrhea), encopresis, recurrent abdominal pain, gastroesophageal reflux, and vomiting or food aversion. On these bases, the evaluable target study population (see Table 1 for inclusion/exclusion criteria) will be divided into four groups (depending on their clinical outcome: neuro competent at-risk infants with (NC-GI) and without GI symptoms (NC), ASD infants with GI symptoms (ASD-GI) and ASD infants without GI symptoms (ASD)). Maternal and paternal genomic samples will be taken from parents of infants at the time of enrollment and analyzed to examine inherited and de novo genetic traits.

Autism Diagnostic Observation Schedule (ADOS Toddler) evaluation [54] will be conducted every 6 months by a trained physician, starting at 12 months of age. For children younger than 24 months who test positive in the ADOS Toddler evaluation, the evaluation will be repeated one month later to confirm diagnosis to enroll the infant in an interventional study, and will be used to divide the participants into two groups: ASD children or non-ASD children (typically developing). Typically developing children will be followed until 36 months (see Figure 3) of age and their data will be selected at the end of the study to provide the information for the matched control comparisons.

Additional behavioral assessments include Early Screening for Autism and Communication Disorders and Repetitive Behavior Scale [55,56], Mullen Scales of Early Learning (MSEL) [57], and Vineland Adaptive Behavior Scales (VABS) [58]. These assessments will take place at 24 and 36 months of age.

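### A 20% drop-off from 600 infants leaves 480, not about 500, and the expected 73 ASD and 44 ASD-GI cases are computed from the 500

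*Protocol article*

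**What the plan says.** All of the planning figures are in the protocol article.

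- **Enrolment.** Section 2.2.1 (Participants): "GEMMA aims to enroll 600 infants younger than 6 months/26 weeks of age". Section 2.2.2 (Observational Trial) says "each site will target recruitment of 200 infants at high risk of developing ASD". Section 2.2.1 names three centres, so this again gives 600, and the caption of Figure 3 repeats that total.
- **Attrition.** Section 4.2 (Power Analysis): "We estimated a conservative drop-off of 20% based on our previous experience with similar projects". The experience cited is two earlier at-risk cohorts, one with 20% loss over 10 years and "a second that has been followed up to 7 years with a 12% drop-off". The rate adopted is 20%.
- **Final cohort.** The next sentence of section 4.2: "The final cohort will comprise approximately 500 at-risk infants".
- **Expected cases.** "Expected prevalence of ASD at 18–24 months in first-degree relatives is 14.7% [9], so in this study we estimate 73 ASD diagnoses". Section 4.2 then applies a 60% prevalence of gastrointestinal symptoms and expects 44 of the 73 to have them.

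The article mentions no replacement of drop-outs, no recruitment beyond 600 and no other attrition rate adopted for planning.

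**The concern.** Two consecutive sentences of section 4.2 cannot both hold at an enrolment of 600. The first sets the loss at 20%; the second gives a cohort that would remain only if the loss were nearer 17%. The plan is therefore slightly less cautious than the word it uses for its own assumption.

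The 500 is also the base for the two case counts that follow. Those counts are the only quantities under the power heading. In this document they are the numerical support for splitting the cohort by ASD and gastrointestinal status (section 2.2.2) and for the pool of diagnosed children from which the interventional trial recruits (section 2.2.3). A base that is too high passes its excess to each of them.

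**Working it through.** **Inputs.** Enrolled N = 600 (sections 2.2.1 and 2.2.2, Figure 3 caption). From section 4.2: drop-off d = 0.20, ASD prevalence 0.147, prevalence of gastrointestinal symptoms in ASD 0.60.

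**1. Reproduce the stated case counts.**
- 500 × 0.147 = 73.5 (stated: 73)
- 73 × 0.60 = 43.8, or 73.5 × 0.60 = 44.1 (stated: 44)

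Both follow from 500, so these two steps are sound and the fault lies before them.

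**2. Check the step from 600 to 500.** Retained = N × (1 − d).
- 600 × 0.80 = 480
- Loss implied by 500: 1 − 500/600 = 16.7%
- Enrolment needed for 500 at 20% loss: 500/0.80 = 625
- At the 12% of the second earlier cohort: 600 × 0.88 = 528

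Neither cited drop-off rate gives 500. Dividing instead of multiplying does: 600/1.2 = 500 exactly. That is a plausible origin of the figure, but the text does not show it.

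**3. Carry 480 forward at the article's rates.**

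| Quantity | Stated | From 480 | Excess in stated figure |
|---|---|---|---|
| Final cohort | about 500 | 480 | 20 |
| ASD | 73 | 480 × 0.147 = 70.6 | 2.4 |
| ASD-GI | 44 | 70.56 × 0.60 = 42.3 | 1.7 |
| ASD without GI symptoms | 73 − 44 = 29 (by subtraction) | 70.56 × 0.40 = 28.2 | 0.8 |

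The last row is rounded from 28.2. Subtracting the rounded 42 from the rounded 71 would give 29, which is rounding only.

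**4. Does it matter downstream?**
- Chance variation in the ASD count at 480: √(480 × 0.147 × 0.853) = 7.8. The shift of 2.4 is about 0.3 of one standard deviation.
- Interventional trial: a minimum of 40 needs 40/73 = 55% of ASD cases to enrol at the stated count and 40/71 = 56% at the corrected count.
- Detectable difference, purely as a gauge of the shift and assuming two-sided 5% and 80% power (the article states neither a power nor an effect size): (1.96 + 0.842) × √(1/n₁ + 1/n₂). For ASD against non-ASD, 73 v 427 gives 0.355 SD and 71 v 409 gives 0.360 SD. For ASD-GI against ASD without GI symptoms, 44 v 29 gives 0.67 SD and 42 v 28 gives 0.68 SD. The slip moves these by about 0.005 and 0.014 SD.

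**The case against.** **The figure is labelled approximate, and the gap is 4% of 500.** That is true, and it limits the consequence. It does not remove the contradiction, because the next step uses 500 as an exact base: a prevalence given to three digits is applied to it and reported as whole children.

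**The two earlier cohorts span 12% to 20% loss, so 528 to 480 infants, and 500 lies inside.** Also true. But section 4.2 does not plan on a range; it adopts 20%. If something in between was meant, the article should say so.

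**The case counts may not be too high in reality.** ADOS assessment starts at 12 months and is repeated every 6 months, the 14.7% refers to 18–24 months, and follow-up runs to 36 months. A child diagnosed and lost later still counts as a diagnosis, and the 20% comes from a cohort followed for 10 years. This stands as a caution: the true yield could reach or exceed 73. However, the article itself applies the prevalence to the cohort left after drop-off, and on that method its figures should start from 480.

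**A reader might infer more: that the study is underpowered, or that the interventional trial cannot be filled.** The documents do not support this. Section 4.2 states no power, significance level or effect size for these counts, so there is no power claim to contradict, and about 71 cases exceed 40 much as 73 do. Nor is it a fault that an article omits detectable differences, or leaves the ASD group without GI symptoms to be found by subtraction; such detail may sit in the full protocol or analysis plan, which are not shown.

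**Conclusion.** The point holds as a small internal error. With 600 enrolled and the adopted 20% drop-off, the final cohort is 480, and the stated 500 corresponds to about 16.7% loss. The 73 and 44 carry the excess. On the article's own rates they become about 71 and 42, leaving about 28 ASD children without gastrointestinal symptoms.

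The size is 20 infants, two to three ASD cases and about two ASD-GI cases, well inside the chance variation of the ASD count. No design decision that the article states depends on it.

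The conclusion takes 600, 20%, 14.7% and 60% as the article gives them and follows its order of applying prevalence after drop-off. It does not say that 20% is the right attrition rate, or that fewer than 73 diagnoses will be observed.

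**What to change.** In section 4.2, make the attrition rate and the cohort size agree, by one of two routes:

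- **Keep 20%.** Restate the final cohort as about 480, ASD diagnoses as about 71 and ASD-GI as about 42, leaving about 28 ASD without gastrointestinal symptoms.
- **Keep 500.** State a drop-off of about 17% in place of 20% and justify it from the earlier cohorts. The 73 and 44 then stand.

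Enrolment stays at 600 under either route, and no detectable-difference figures need to be added. The cost is an edit to one paragraph. Under the first route the stated figures become slightly less favourable; under the second, the attrition assumption becomes slightly less cautious. If the same figures appear in the full protocol or analysis plan, they should be changed there as well.

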### 4.3. Developing an Integrative Multilevel Model to Predict ASD

Path a: A causal path between the genetics and the final effect on the onset of ASD, with the microbiome as the mediator (a1 × a2), so that the intestinal microbiome will be altered for the genetics to ultimately influence the development of the disorder (microbiome-mediated epigenetic pressure).

Path b: A causal path of the microbiome’s effect on ASD mediated (b1 × b2) by the metabolic activity of intestinal bacteria, which, through the production of metabolites, affects the intestinal transcriptome and proteome. Including a bidirectional path between microbiome and metabolomics to capture how metabolism could alter the microbial metabolism and ultimately the risk for ASD.

Path c: A bidirectional path between the transcriptome and the microbiome because their causal relationship will depend on each other.

Path d: A direct relationship between lifestyle factors and the onset of the disorder mediated (d1 × d2) by alterations in the microbiome.

Path e: The environment affecting the onset of the disorder as a mediator and affecting the composition of the microbiome and resulting metabolome, in turn, influencing gene and protein expression.

Full Model: Time points will be clustered within individual characteristics; analyzing all of the paths listed above, individuals will be clustered within families, and families within regions.

## 5. Discussions and Conclusions

The implementation of primary prevention strategies for ASD via manipulation of the intestinal microbiota represents a complete paradigm shift of treatment and prevention of ASD. The identification of specific ASD metagenomics and metabolomics phenotypes can also help to define additional biomarker-based diagnostic tools and therapeutic interventions. Additionally, GEMMA’s biorepository will encourage future epigenetic studies and validation of biomarkers. Our findings may also impact the prevention and treatment of other neuroinflammatory conditions.

## Figures and Tables

**Figure 1 brainsci-10-00743-f001:**
[figure not shown]
GEMMA (Genome, Environment, Microbiome and Metabolome in Autism) study design.

**Figure 2 brainsci-10-00743-f002:**
[figure not shown]
Preclinical studies—development of humanized mouse models by transplanting fecal samples from a well-characterized ASD diagnosed proband (and sibling controls). Four groups of children, each with 4 children, recruited in one center in Europe (Italy): autistic with no GI problems, autistic with GI problems, controls without or with GI problems. Ongoing.

**Figure 3 brainsci-10-00743-f003:**
[figure not shown]
Clinical trials—prospective multi-center observational study evaluating infants at risk of ASD. 600 infants—newborns, less than 6 months of age—at risk, i.e., first-degree relatives of ASD individuals, recruited in US, Italy, and Ireland (200 infants at each site, over a 3-year period). Ongoing.

**Figure 4 brainsci-10-00743-f004:**
[figure not shown]
Interventional trial—prospective, multi-center, open-label, uncontrolled study to evaluate the effects of pre/pro/synbiotics supplementation in infants with a diagnosis of ASD. Forty children between the ages of 18 and 36 months diagnosed with ASD from the observational trial will be recruited (with parental consent).

**Table 1 brainsci-10-00743-t001:** Inclusion and exclusion criteria for the observational trial.

Inclusion Criteria (All Must be Met)	Exclusion Criteria (Participant Will be Excluded from the Study if Any of the Criteria are Met)
Healthy newborns or infants First-degree relatives of ASD participant (at least one sibling affected by ASD) Younger than 6 months/26 weeks Have never received solid food (elementary formula feeding permitted)	Newborns with significant health issues that require surgical treatments or continuous medical treatments and/or surgical treatments Infants older than 6 months/26 weeks Infants who have been introduced to solid food (including occasional use) Severe GI problems requiring immediate treatment (life-threatening) Severely underweight/malnourished children Dietary restriction in the previous 3 months Tube feeding Drugs since birth which may affect the biomarkers being assessed, for example Antibiotics within one month prior to enrollment; antibiotics used as a continuous course for ≥28 days prior to enrolment
